#### *Diagnostic value of bedside US and advanced US in diagnosing pyelonephritis*

The radiological findings will be described systematically using standardized assessment templates for bedside US, advanced US, and MRI. The project assistant will describe the bedside US findings, and radiologists will describe the advanced US and MRI findings with standardized relevant clinical information. The US operators and the MRI-operator will be blinded to the results of each other. Study consultants with experience in kidney imaging will post-process describe the scans and video clips systematically using developed research templates.

A reference diagnose for pyelonephritis is defined by a panel of experts. The experts are two consultants from Emergency Departments, who will determine the final diagnoses based on all available relevant information including e.g. results of imaging, blood sample and clinical information. A standardized template will be used. Conflicts will be discussed until consensus is reached.

The results from bedside US and advanced US of kidney are compared with results from the MRI and reference diagnose. The advantages and disadvantages of the diagnostic capability of the individual modalities are described.

It is assumed that the reference diagnose finds 98% of patients and index test 90%. With a power of 80%, at least 132 patients must be included (one-sided McNemar test).

Primary outcome is sensitivity and specificity, LLR+, LLR-, ROC curve and AUC for diagnosing pyelonephritis. To test the hypothesis a chi-squared test will be performed.

#### *Effect of POC-PCR on antibiotic prescription*

The antibiotic prescribed in the 4-hour plan, will be collected. The antibiotic type will be classified in four groups; 1) no antibiotic prescription, 2) narrow spectrum antibiotics, 3) broad spectrum antibiotics and 4) broad spectrum antibiotics not targeting pneumonia treatment. The primary outcome is to investigate difference in type of antibiotic prescription in the three randomization groups.

Secondary outcomes include revision of antibiotic treatment at 48 hours, registered adverse events (e.g. length of stay, in-hospital mortality, 30-days mortality and clostridium infections), and agreement between POC-PCR results and results of sputum culture.

To achieve a power of 82% for the main analysis, 200 patients with suspected CAP must be included. Generalized mixed effect models will be adjusted for strong predictors. If the sample size is not sufficient for a generalized mixed effect models the corresponding univariate analysis will be conducted

*Amendment:* Intervention group: sputum samples analysed by POC-PCR. Control group: routine microbiology analysis. It is a superiority randomized trial. Primary outcome is targeted versus non-targeted antibiotic treatment prescribed at four hours after admission. Targeted treatment is defined as narrow spectrum antibiotics directed against CAP, antibiotics directed against a detected respiratory pathogen or no antibiotics (e.g. in the absence of a bacterial pathogen and/or presence of a viral pathogen). Non-targeted treatment is defined as broad spectrum antibiotics not directed against a specific pathogen or antibiotics not directed against CAP. (Appendix VI - Algorithm for antibiotic treatment). The analyses will follow the intention-to-treat principal and a hierarchical mixed effect logistic model will be utilized to analyze the primary outcome to accommodate the hierarchical structure of the random effect, which manifest according to different personnel collecting the samples and geographical variation.

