## Setting

The study will recruit patients from here regional hospitals in the Region of Southern Denmark: the ED in Kolding, Lillebælt Hospital, the ED in Aabenraa, Hospital Sønderjylland, and the ED in Odense, Odense University Hospital. Six study assistants are associated to the study to ensure patient recruitment and data collection. They will be trained and certified in US of lung and kidneys (Objective Structured Assessment of Ultrasound Skills (OASUS) test), sputum collection, operation and integration of POC-PCR as well as POC urine flow cytometry.

Enrollment to the study commences from February 2021, and continues until the predefined sample size has been reached, which is estimated to be no longer than eight months. The last patient is expected to be enrolled in the end of September 2021. The patients will be enrolled from Sunday to Friday 10am-8pm except on holidays.

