**Table 1 Information to be obtained from the medical record**

| Time of collection       | Variables i medical record                                             | Purpose                            |
|--------------------------|------------------------------------------------------------------------|------------------------------------|
| Prior ED arrival         | Antibiotic treatment within last 6 months                              | Confounding                        |
| Upon ED arrival          | Vital signs                                                            | Patient characteristic             |
|                          | Triage                                                                 | Patient characteristic             |
|                          | Comorbidity                                                            | Patient characteristic             |
|                          | Antibiotic allergy                                                     | Patient characteristic             |
|                          | Inhalation medication                                                  | Confounding                        |
| During admission         | Prescribed antibiotic                                                  | Outcome                            |
|                          | Blood test results                                                     | Patient characteristic             |
|                          | Microbiological test results of blood, urine, swab and sputum          | Outcome                            |
|                          | Diagnostic imaging results                                             | Outcome                            |
|                          | ICU transfer                                                           | Outcome                            |
|                          | Findings regarding diagnosis and treatment described in clinical notes | Outcome and patient characteristic |
|                          | Date of discharge                                                      | Outcome                            |
| After hospital discharge | Date of mortality                                                      | Outcome                            |
|                          | Date of readmission                                                    | Outcome                            |

|  |                   |         |
|--|-------------------|---------|

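### The fallback for the POC-PCR primary analysis drops hospital and the chosen predictors together, although only the random effects are hard to estimate

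*Protocol*

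**What the plan says.** The section Effect of POC-PCR on antibiotic prescription holds two layers of text. The paragraphs before the amendment give the sample size, "To achieve a power of 82% for the main analysis, 200 patients with suspected CAP must be included", the model, "Generalized mixed effect models will be adjusted for strong predictors", and the fallback, "If the sample size is not sufficient for a generalized mixed effect models the corresponding univariate analysis will be conducted". The predictors are not named, and no criterion for an insufficient sample is given.

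The amendment makes the outcome binary: "Primary outcome is targeted versus non-targeted antibiotic treatment prescribed at four hours after admission". It says that "a hierarchical mixed effect logistic model will be utilized to analyze the primary outcome", to allow for the "hierarchical structure of the random effect, which manifest according to different personnel collecting the samples and geographical variation". It mentions neither covariates nor a fallback.

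On the number of clusters, Setting names three emergency departments and says "Six study assistants are associated to the study to ensure patient recruitment and data collection". On available covariates, Table 1 lists "Antibiotic treatment within last 6 months" with confounding as its purpose. Inhalation medication has the same label, and triage, vital signs, comorbidity and antibiotic allergy are listed as patient characteristics.

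**The concern.** A univariate analysis has arm as its only term. Falling back to it removes the random effects, the hospital term and every selected predictor in one step. The weak part of the amended model is the random part: one variance would rest on three hospitals and the other on about six people. A fixed three-level hospital factor and a few baseline covariates do not share that weakness. The Protocol offers nothing between the full model and no adjustment.

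Two things are at stake. One is the precision that the predictors would have bought; the plan itself calls them strong. The other is the meaning of the reported effect. The odds ratio is non-collapsible, so a mixed logistic model and a univariate one estimate different odds ratios even when both are correct. Because the trigger is undefined, which of the two is reported is left to judgement.

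**Working it through.** **Inputs.** From the Protocol: 200 patients, 82% power, 1:1 allocation to two groups, three hospitals, six study assistants. Not given for this comparison: control rate, effect size, alpha, sidedness and prognostic strength. Assumed: two-sided alpha 0.05, 100 per arm.

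**Step 1: what the 82% is consistent with.** It cannot be reproduced without rates. With power = Φ[(d − 1.96·SE0)/SE1], where SE0 is the pooled and SE1 the unpooled standard error:

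- 40% vs 60%: SE0 = √(2·0.5·0.5/100) = 0.0707, SE1 = √(0.24/100 + 0.24/100) = 0.0693. Power = Φ[(0.20 − 0.1386)/0.0693] = Φ(0.886) = 81.2%.
- 30% vs 50%: SE0 = 0.0693, SE1 = 0.0678. Power = Φ[(0.20 − 0.1358)/0.0678] = Φ(0.947) = 82.8%.

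For control rates from 10% to 60%, 82% power corresponds to differences of about 15 to 20 percentage points. The 40% vs 60% case is carried forward as a working assumption. Its marginal odds ratio is (0.6/0.4)/(0.4/0.6) = 2.25.

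**Step 2: power and odds ratio with and without adjustment.** Simulation with 4,000 trials per scenario, 200 patients, three sites and marginal rates held at 40% vs 60%. The adjusted model has site as a fixed factor (standing in for the random effects) plus, in the first four rows, one baseline predictor. SDs are on the logit scale and all are assumed. The Monte Carlo standard error is about √(0.82·0.18/4000) = 0.6 points.

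| Site SD | Predictor SD | Power, univariate | Power, adjusted | Gain, points (rounded) | Conditional OR | Marginal OR |
|---|---|---|---|---|---|---|
| 0 | 0 | 82% | 81% | −2 | 2.25 | 2.25 |
| 0.3 | 0.5 | 83% | 84% | +1 | 2.40 | 2.25 |
| 0.5 | 1.0 | 83% | 88% | +5 | 2.76 | 2.25 |
| 0.5 | 1.5 | 82% | 93% | +11 | 3.23 | 2.25 |
| 0.3 | none | 83% | 82% | −1 | 2.29 | 2.25 |
| 0.5 | none | 83% | 84% | +1 | 2.37 | 2.25 |
| 0.8 | none | 82% | 87% | +4 | 2.56 | 2.25 |

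Gains are taken before the powers are rounded.

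**Step 3: validity.** With no treatment effect, site SD 0.5 and predictor SD 1.0, the rejection rate was 4.8% for the univariate and 4.8% for the adjusted analysis.

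**Step 4: which model the 82% belongs to.** The Protocol attaches it to the main analysis without saying whether that is adjusted. If it was computed unadjusted, the fallback delivers the stated power and forgoes a gain. If it was computed for the adjusted model, a linear approximation with Φ⁻¹(0.82) = 0.915 gives fallback power Φ[(1.96 + 0.915)·√(1 − R²) − 1.96]. That is Φ(0.768) = 78% at R² = 0.10 and Φ(0.612) = 73% at R² = 0.20. Both R² values are assumptions.

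**Step 5: can 200 patients carry the simpler adjusted model?** Arm (1), hospital (2) and, say, three predictors make six coefficients. At 40% vs 60% there are about 100 events and 100 non-events, or 100/6 ≈ 17 per coefficient. At 10% vs 25.4% there are about 100·(0.10 + 0.254) ≈ 35 events, or about 6 per coefficient. The model is comfortable at middling rates. At a low rate, the covariate list must be kept short.

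**The case against.** The strongest objection is that the fallback and the strong predictors stand in text that predates the amendment, next to three randomisation groups and a four-category outcome. The amendment restates the arms, outcome and model without either. If the amended text alone governs, only hospital and collector are at stake, and hospital alone moved power by −1 to +4 points. This is a fair limit on the size of the problem. It does not remove it, because the fallback sentence was never withdrawn.

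A reader might infer that the fallback is likely to be used. In a simulation of 300 trials with assumed logit SDs of 0.5 (hospital) and 0.3 (collector) and two collectors per hospital, at least one variance was estimated near zero in 73% of trials. That is not the chance of triggering the rule. The stated trigger is insufficient sample size, a zero variance still leaves a fitted model with its fixed terms, and the Protocol states neither the SDs nor two collectors per hospital. Nor does it say that only the study assistants collect sputum. It is also an inference that sufficiency would be judged after seeing outcomes; it could be judged on enrolment alone.

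A reader might also infer bias, or the loss of every baseline variable collected. Neither is supported. Randomisation keeps the univariate test valid, and the plan would adjust only for predictors judged strong.

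Finally, covariate lists and convergence steps commonly belong in a statistical analysis plan, which is not at hand. Their absence is not the criticism here. The Protocol itself states a replacement rule, and that rule is inferior to one that its own data allow. It is also true that this section names no effect measure, so the switch between odds ratios matters only if an odds ratio is what is reported.

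**Conclusion.** The point holds as a matter of efficiency and of what is estimated, not of bias. The Protocol keeps a rule that, if used, discards hospital and the selected predictors to solve a problem confined to the random effects. Under assumed rates of 40% vs 60%, two-sided 0.05 and 100 per arm, the power given up is about zero if the predictors are weak, 1 to 5 points if moderate and about 11 if strong. The odds ratio shifts from about 2.4 to 3.2 (conditional) to 2.25 (marginal), and that gap also shrinks as the predictors weaken. The Protocol gives no prognostic strength, so the place on this range is unknown. So is the probability that the fallback is used. The document also leaves open whether the fallback survives the amendment, and that should be settled. This is worth changing, but it does not threaten the trial's validity.

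**What to change.** Replace the fallback sentence, and state that the replacement applies to the amended binary outcome:

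- If the mixed logistic model does not converge, or a random-effect variance is estimated as zero, drop only the random effect that fails. Fit a logistic regression of targeted treatment on arm, with hospital as a fixed three-level factor and the same short list of baseline predictors. Keep the collector random intercept if it is not the term that failed.
- Name the predictors before outcome data are examined, from variables already collected. Antibiotics in the previous six months, labelled as confounding in Table 1, is one candidate.
- Report one effect measure whichever model is fitted, such as the standardised risk difference, so that its meaning does not depend on whether a variance could be estimated.
- Keep the unadjusted comparison as a sensitivity analysis.

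The cost is wording, a few extra parameters and the need to commit to covariates in advance. No new data are needed. If the predictors prove uninformative, adjustment may cost a point or two of power, as the first row of the table shows.

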### *Diagnostic value of POC urine flow cytometry*

Common urinary culture shows significant growth of uropathogenic bacterium in approximately 50% of people with suspected pyelonephritis (30). Asymptomatic bacteriuria accounts for about 20% in the elderly population, depending on gender and age (46), which among 1000 inpatients suspected of infection, of which 15% have pyelonephritis, gives a sensitivity of 50% (95% CI: 42-58 %) and a negative predictive value of 90% (95% CI: 77-83%). With the expectation of identifying at least 150 cases of pyelonephritis among 750 inpatients suspected of infection, an improvement in sensitivity to 70% (95% CI: 62-77%) and negative predictive value to 95% (95% CI: 93 -96%) could be found with 95% security.

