### ***Hypothesis, aim and objectives***

Our broad hypothesis is that by improving the knowledge of ED infected patients and by introducing new diagnostic tools, which contribute to the development of rapid and more accurate diagnosis of acute infections, a more appropriate antibiotic therapy can be administered.

The project aims to adapt and evaluate alternative diagnostic tools and working methods that support a prompt and accurate diagnosis of hospitalized patients suspected of an urgent infection – with special focus on pneumonia and acute pyelonephritis.

The research objectives are:

- 1) What is the patient characteristics and course of treatment of the different ED infections?
- 2) What is the diagnostic value of the infection markers PCT, suPAR, and CRP in patients with suspected pneumonia and pyelonephritis?
- 3) What is the diagnostic value of the lung injury markers SP-D, YKL-40, and KL-6 on diagnosing pneumonia
- 4) What is the impact of bedside-US and ULDCT on diagnosing pneumonia ?
- 5) What is the impact of advanced US on diagnosing pyelonephritis?
- 6) What is the impact of bedside-US on diagnosing hydronephrosis?
- 7) What is the impact of POC-PCR analysis of sputum on antibiotic prescriptions?
- 8) What is the impact of POC urinary flow cytometry on diagnosing and excluding bacteraemia?

The goal is to combine the results of all these eight objectives into one novel diagnostic model which the ED physician can apply when patients with suspicion of an infection is admitted.

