#### ***POC urine flow cytometry***

Within 4 hours from arrival, a urine sample will be collected according to routine procedure. The study assistant will be responsible for the collection to optimize compliance. Preferably a mid-ray urine or for catheter users (if possible) by introducing a clean catheter for optimal urine quality. The sample will be divided into two aliquots; one half for routine urine culturing in the Microbiological Department, and one half for POC urine flow cytometry analysis in the Biochemical Department.

The POC urine flow analysis is performed by the Sysmex UF -5000, a fully automated flow cytometry analyser for particle analysis in urine. It discriminates and counts 17 diagnostic parameters of cells and formed elements in urine. Particles are stained by specific flouorochromes for nucleic acids and for surface structures, and are exposed to a blue semi-conductor laser-light at 488 nm wavelength. Counting and classification is based on signals of forward scattered light (FSC), side scattered light (SSC), side fluorescent light (SFL), and depolarized side scattered light (DSS). The pattern of individual light signals is translated by algorithms allowing identification and classification into the particle categories, and results will be collected for bacteria, White Blood Cells (WBC), and Red Blood Cells (RBC). The light signals differ for Gram negatives and Gram positives, and this can be recognized by the analyser. For the above mentioned parameters, the analytical performance of the urine flow cytometer will be compared to the gold standard a urine culture on selective agar plates. A protocolled procedure for the collection and handling of samples will ensure consistent data quality.

The analysis will be carried out by laboratory assistants. The results of the POC urine flow cytometry analysis are not currently reckoned state-of-the-art and will be used for scientific purpose only. Results will be coded by the laboratory technician and not visible in the electronic laboratory system.

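### Two negative predictive values in the flow-cytometry planning text are wrong: the baseline interval excludes its own estimate, and the 95% target exceeds the 93.0% ceiling set by the stated inputs

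*Protocol*

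**What the plan says.** The planning figures for the flow-cytometry objective are in *Diagnostic value of POC urine flow cytometry*.

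- **Baseline.** The setting is "among 1000 inpatients suspected of infection, of which 15% have pyelonephritis". The section takes culture growth in about half of suspected pyelonephritis and adds that "Asymptomatic bacteriuria accounts for about 20% in the elderly population". It concludes that this "gives a sensitivity of 50% (95% CI: 42-58" per cent) and "a negative predictive value of 90% (95% CI: 77-83" per cent). No specificity is stated.
- **Target.** The section then expects "at least 150 cases of pyelonephritis among 750 inpatients suspected of infection" and claims that a sensitivity of 70% (62-77%) and a rise in "negative predictive value to 95% (95% CI: 93 -96%) could be found with 95% security".

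Elsewhere, the opening of *Outcomes and statistical analysis* plans at least 1000 patients, at least 150 of them with pyelonephritis. The procedure section *POC urine flow cytometry* says that the analytical performance of the analyser "will be compared to the gold standard a urine culture on selective agar plates". Objective 8 asks "What is the impact of POC urinary flow cytometry on diagnosing and excluding bacteraemia", whereas *Etiological diagnostics* in the Background presents the test as a way to exclude bacteriuria.

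**The concern.** A 95% confidence interval has to contain its own point estimate, and 77-83% does not contain 90%. The target has a different fault. NPV is fixed by sensitivity, specificity and prevalence, and moving from 1000 to 750 patients with the same 150 cases raises the prevalence. That lowers the highest NPV that a 70% sensitivity allows.

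The Background promotes flow cytometry as a rule-out test, so NPV is the quantity a reader will look at first. This section is the only precision justification given for objective 8, and both of its NPV entries fail. A reader would take away an improvement from 90% to 95% that the stated patient numbers do not deliver.

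**Working it through.** **Inputs, all from *Diagnostic value of POC urine flow cytometry***

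- Baseline: 1000 patients, 15% cases, so 150 cases and 850 non-cases; sensitivity 50%.
- Implied specificity at baseline: 80%, inferred from the 20% asymptomatic bacteriuria. The section does not state it.
- Target: at least 150 cases among 750 patients, so at most 600 non-cases; sensitivity 70%.

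**Formulas**

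- TN = specificity × non-cases
- FN = (1 − sensitivity) × cases
- NPV = TN / (TN + FN)

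Intervals were computed by the Wald, Wilson and exact methods.

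**Step 1: figures that reproduce**

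- Baseline sensitivity: 75/150 = 50%, Wald 42.0-58.0%. Agrees with the protocol.
- Target sensitivity: 105/150 = 70%, exact 62.0-77.2%. Agrees.
- Baseline NPV, point estimate: TN = 0.80 × 850 = 680 and FN = 0.50 × 150 = 75, so NPV = 680/755 = 90.1%. Agrees with 90%.

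**Step 2: baseline NPV interval**

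- For 680/755: Wald 87.9-92.2%, Wilson 87.7-92.0%, exact 87.7-92.1%. All round to 88-92%.
- For the implied specificity, 680/850 = 80.0%: Wald 77.3-82.7%, Wilson 77.2-82.6%. This rounds to the printed 77-83%.

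The likeliest explanation is that the specificity interval was printed beside the NPV. That is an inference. The mismatch itself needs no explanation to be an error.

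**Step 3: target NPV on the stated inputs**

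FN = 0.30 × 150 = 45. The most favourable case is perfect specificity, TN = 600:

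NPV ≤ 600 / (600 + 45) = 93.0% (Wilson 90.8-94.7%).

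This ceiling needs no assumption about specificity. More than 150 cases among 750 lowers it; with 160 cases, for example, it is 590 / (590 + 48) = 92.5%. At 80% specificity, NPV = 480/525 = 91.4% (about 89-94%).

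To reach 95% with 150 cases among 750, FN must not exceed TN × (1/0.95 − 1):

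- specificity 100%: FN ≤ 600 × 0.0526 = 31.6, so sensitivity of at least 78.9%;
- specificity 80%: FN ≤ 480 × 0.0526 = 25.3, so sensitivity of at least 83.2%.

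**Step 4: which inputs would give 95% (93-96%) at 70% sensitivity?**

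| Cases / patients | Specificity | NPV |
|---|---|---|
| 150 / 1000 | 80% | 680/725 = 93.8% (92-95%) |
| 150 / 1000 | 91% | 773.5/818.5 = 94.5% |
| 150 / 1000 | 100% | 850/895 = 95.0% (93-96%) |
| 150 cases plus 750 non-cases | 100% | 750/795 = 94.3% |
| 112.5 / 750 (15%) | 100% | 637.5/671.25 = 95.0% |

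The stated value fits a 15% prevalence with a specificity of roughly 91% or more. It does not fit 150 among 750, and even the generous reading of 150 cases plus 750 non-cases falls short.

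**Step 5: like for like**

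The baseline prevalence is 150/1000 = 15% and the target prevalence is 150/750 = 20%. At 50% sensitivity and 80% specificity, the baseline NPV for 150 among 750 would be 480/555 = 86.5%, not 90%. The printed change from 90% to 95% therefore mixes a change of test with a change of population.

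**The case against.** The strongest reply is that these are slips in planning text with little hanging on them. The plan for at least 1000 patients and 150 pyelonephritis cases does not rest on the NPV figures, no decision rule uses an NPV of 95%, and flow-cytometry results are kept from the treating physicians. The sensitivity half of the claim reproduces. All of that stands. It limits the importance of the point but does not make either NPV entry right.

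Four stronger readings are tempting, and the document does not support them.

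- *A reader might infer that an NPV of 95% is out of reach and should be deleted.* With 150 cases among 1000, it is reached to the nearest per cent at 70% sensitivity if specificity is about 91% or more. The protocol states no specificity for flow cytometry; the 80% comes from background on bacteriuria, and carrying it to the new test is an assumption.
- *A reader might infer that the true gain is smaller than claimed.* That depends on the denominator. With 150 among 750 and 80% specificity at both steps, NPV moves from 86.5% to 91.4%, a gain of 4.9 points. The levels are wrong; the size of the gain need not be.
- *A reader might compare the 1000-patient intervals at 80% specificity (87.7-92.0% and 91.8-95.3%) and call the difference undetectable because they overlap.* One urine sample is split between culture and flow cytometry, so the data are paired, and comparing two separate intervals is not the relevant test.
- *A reader might infer that improving on culture cannot be tested because culture is the gold standard.* The procedure section limits that standard to analytical performance. The planning section concerns pyelonephritis, for which the imaging section on pyelonephritis defines an expert-panel reference. These can be two separate questions.

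**Conclusion.** The point holds for two entries. The interval of 77-83% is wrong for an NPV of 90%; about 88-92% is right, given the implied 80% specificity that also reproduces the 90%. The target NPV of 95% is unattainable with 70% sensitivity and at least 150 cases among 750 patients: the ceiling is 93.0%, whatever the specificity. The claim of 95% security therefore fails for the NPV on the stated inputs, while the sensitivity figures stand. The baseline and target are also not like for like, and the 750 departs from the study-level plan of at least 1000.

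This is a correction to the planning text of one of eight objectives. It does not show that the study is too small, and it does not change the recruitment target.

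**What to change.** In *Diagnostic value of POC urine flow cytometry*:

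1. Replace the baseline NPV interval with about 88-92%, and state the 80% specificity on which the 90% rests.
2. Use one denominator and one prevalence for both steps, consistent with the opening of *Outcomes and statistical analysis*.
3. State the specificity assumed for flow cytometry and restate the target NPV and its interval from it, using the 150-among-1000 values tabulated above. If 150 among 750 is kept, state no more than 93.0% and recompute the baseline for the same population.

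As a minor wording point, reconcile the target condition in objective 8 (bacteraemia) with the bacteriuria named in the Background and the urine-culture comparison in the procedure section.

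The cost is protocol wording only: no extra patients, samples or procedures.
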